**Principal Investigator Signature: _____________ Date: ________________**

**Abstract**

**Background**: Cancer-related cognitive impairment (CRCI) is commonly experienced by individuals with non-central nervous system cancer due to the disease and treatment trajectory. CRCI has been mainly studied post chemotherapy and has found to include many cognitive impairments among them executive functions. Executive functions are high cognitive functions that include abilities such as (working memory, initiative, inhibition...). Impairments in executive functions can disrupt functioning and participation in complex daily activities such as cooking, driving that involve multitasking and coping with novel situations. These deficits impact person's persons social participation, work and quality of life, in addition to managing their medical condition after cancer. The association between objective and subjective cognitive complaints is still unclear and might be related to psychological aspects. In addition, there is currently no objective, functional, occupation-based assessment that detects the subtle mild cognitive changes particularly associated with CRCI. This raises the need for robust clinical testing of cognitive impairment in patients recently diagnosed with cancer, in order to guide clinicians in creating early individualized treatment plans. **Therefore, we aim to** explore changes in executive functioning and daily functioning following chemotherapy among individuals with non-central nervous system cancers. The specific aims are: 1) to compare executive functioning (objective and perceived), daily functioning, emotional status and fatigue pre versus post chemotherapy; 2) pre and post chemotherapy to determine which variables (executive functioning, emotional status, fatigue) best explain daily functioning. **Methods:** Fifty participants will be included aged between 18-75 years, newly diagnosed with a primary non-central nervous system malignancy (lung, breast, colon, ulcer, urinary tract, canine tumors) stages I-III pre- commencement of adjuvant (post-surgery) or neoadjuvant (prior to surgery) chemotherapy from the oncology department at Bnai-Zion Medical Center. A mixed-methods pre-post experimental design will be conducted. Pre and post chemotherapy cognitive and executive functions assessments and self-report measures will be performed by a qualified occupational therapist, will last up to one hour and will be performed in the oncology department of Bnai-Zion Medical Center. The primary outcome, namely "Functioning in daily activities" will be measured by the Canadian Occupational Performance Measure (COPM) an individualized semi-structured interview and outcome measure of performance and satisfaction with one's performance in daily activities. The secondary outcomes, namely Daily participation will be assessed by the Reintegration to Normal Living index (RNL) questionnaire; Working memory capacity will be assessed by the Backward Digit Span; Dual Tasking will be assessed by performing two tasks concurrently (motor by the Box & Blocks Test and cognitive by backward subtraction for 1 minute); Cognitive flexibility will be assessed by the Color Trail Test; Cognitive performance-based assessment will be assessed by the Weekly Calendar Planning Activity; Perceived cognitive executive functioning and Cognitive Self Efficacy will be assessed by the FACT-Cognitive Function in addition to three open questions; Emotional status will be assessed by the Emotional Well-Being FACT-G (General) questionnaire; Fatigue will be assessed by the Functional Assessment of Chronic Illness Therapy – Fatigue (FACIT-F); in addition to demographic and medical data questionnaire. **Procedure:** Following the approval of Bnai-Zion Medical Center, participants will be recruited by the help of their primary medical oncology staff. Each participant will undergo two assessment sessions; administered pre and post chemotherapy. Assessments will last up to one hour and will be performed in the oncology department of Bnai-Zion Medical Center. **Statistical analysis:** To compare between pre- and post-chemotherapy assessment: for normally distributed variables, paired t-tests or Wilcoxon Signed Ranks will be used; Multivariate linear regression analysis (Enter method) will be used to identify the variables that best explained daily performance (measured by COPM) pre and also post chemotherapy. *Qualitative data analysis* will include participant's answers to the open questions pre and post chemotherapy. Interviews will be analyzed using the phenomenological content analysis method.

**Introduction**

Following chemotherapy, persons living with and beyond cancer (LWBC) deal with short and long-term cognitive deficits (Dietrich and Kaiser, 2016). These deficits have been consistently reported across all cancer types, including cancers that are non-central nervous system (CNS) (Scherling and Smith, 2013) as cognitive related cancer impairment (CRCI). CRCI mainly studied after chemotherapy and includes impairments of short-term and working memory, attention, executive functions and/or processing speed (Hodgson et al., 2012; Li & Caeyenberghs, 2018; Lindner et al., 2014), deteriorated concentration, learning and language problems (Dietrich and Kaiser, 2016). Executive functions are higher cognitive abilities, which are crucial for performing complex daily activities (such as shopping, cooking or driving). Impairments in executive functions can disrupt complex activities and daily occupations that involve multitasking, strategic thinking, planning, and coping with novel situations (Katz & Maeir, 2011). These deficits impact person's occupational and social functioning and quality of life, maintaining work performance and carrying out daily tasks (Myers, 2013; Rust and Davis, 2013) in addition to managing their medical condition after cancer.

The impact of CRCI on everyday activities performance makes it an important area for occupational therapy, however it is relatively unexplored. This could be because neuropsychological tests do not adequately capture the deficits that participants experience in their everyday lives (Hodgson et al., 2013). CRCI is more commonly reported than objectively confirmed in persons living with or beyond cancer (LWBC) (Lange et al., 2019). Although the relation between objective (neuropsychological tests) and subjective (self-reports) complaints is still debated (Bender et al., 2006), self-report questionnaires might have more ecological validity compared to neuropsychological tests, occupational therapists can develop assessment tools and interventions to enable self-management and to enhance quality of life. However, there is currently no objective, functional, occupation-based assessment that detects the subtle mild cognitive changes particularly associated with CRCI.

Recent studies show that a significant portion of persons LWBC with non-central nervous system (CNS) tumors experience cognitive decline prior to treatment, suggesting a role for tumor-derived factors in modulating cognition and behavior (Olson & Marks, 2019). Cognitive complaints are often linked with psychological factors such as anxiety and depression (Menning et al., 2015). In addition to psychological factors also increased levels of fatigue accounted for 72% of the variance in perceived cognitive difficulties (Jenkins et al.,2016). Methodological issues may be a barrier in detecting cognitive deficits. For example, it has been noted that when using cross-sectional data, the inferred deficits may be inflated compared to longitudinal data because comparison to a pre-treatment baseline was not possible (Li & Caeyenberghs, 2018). Therefore, comparison to baseline assessment may allow to determine which impairments resulted from the treatment or was present prior to the commencement of treatment (Hodgson et al., 2013).

Recent clinical studies demonstrate that CRCI is an underappreciated symptom of cancer. These studies emphasize the need for robust clinical testing of cognitive impairment in persons recently diagnosed with cancer, in order to guide clinicians in creating early individualized treatment plans. Therefore, it is essential to characterize the cognitive functioning of adults newly diagnosed with cancer and its impact on patients' daily functioning in order to provide at an optimal timing intervention that aim to prevent cognitive deterioration and its effects on daily functioning.

**The overall aim of this study is** to explore changes in executive functioning and daily performance following chemotherapy among individuals with non-central nervous system cancers. The specific aims are: 1) to compare executive functioning (objective and perceived), daily performance, emotional symptoms and fatigue pre versus post chemotherapy; 2) pre and post chemotherapy to determine which variables (executive functioning, emotional, fatigue) best explain daily functioning

**Hypotheses according to aims:**

# **1a**. Post chemotherapy participant's objective and perceived executive functioning, emotional symptoms and fatigue will significantly worsen compared with pre chemotherapy.

# **2a**. Pre chemotherapy, daily functioning will be mostly explained by higher emotional symptoms and fatigue.

**Study design**

A mixed-methods pre-post experimental design will be conducted.

The assessments will be performed by a qualified occupational therapist.

***Pre chemotherapy assessment***: will be conducted after diagnosis and before commencement of adjuvant or neoadjuvant chemotherapy.

***Post chemotherapy assessment***: will be performed after at least 3 months after commencement of adjuvant or neoadjuvant chemotherapy and within no more than one month after completing chemotherapy (before starting other treatments such as hormonal or biological therapies).

# **CRF and Measures (Appendix 1):**

1. The primary outcome ***"*** ***performance and satisfaction performance in daily activities "*** will be measured bythe Canadian Occupational Performance Measure (COPM) (Law, et al., 1990); an individualized semi-structured interview and outcome measure of performance and satisfaction with one's performance in self-care, productive, leisure and social activities. During the pre-chemotherapy assessment participants identify up to five activities that they prioritize as meaningful for them. Each of these activities is then rated on a 10-point scale for perceived performance (1=not able to do at all, 10=able to do extremely well) and similarly for satisfaction with performance. The final scores of the COPM are the average scores for total performance and for satisfaction. During post chemotherapy assessment, the participants will repeat the COPM for the same activities they prioritized in the pre chemotherapy assessment. The COPM is valid and reliable (Carswell et al., 2004), widely used in research, and was used as the primary outcome measure in an RCT study that examined the effectiveness of an OT intervention with women after breast cancer (Loubani et al., 2022).
2. Secondary outcome measures:
3. *Daily participation* will be assessed by the Reintegration to Normal Living index (RNL; Wood-Dauphinée et al., 1988). The RNL is a questionnaire for evaluating the consequences of a disease and the required therapy on the patient’s life. The RNL has11 statements of participation in recreational and social activities, movement within the community, and degree of comfort the individual has in his/her role in the family and with other relationships. The responses are given on a 1–10-point Likert scale (1, highly do not agree; to 10 highly agree). The adjusted score is calculated as the (Total Score/110) × 100, and ranges from 10–100 points, with a higher score indicating more participation. The RNL has previously been used with patients undergoing surgery and treatment for rectal cancer (O’Connor et al., 2014).
4. Objective executive functioning:

- *Working memory* capacity will be assessed by the Backward Digit Span (**BDS**; Wechsler, 1997). The examiner mentions a series of digits in a forward order, thereafter the participant is asked to repeat the same series of digits in a backward order. The number of correct sequences will be recorded.

- *Dual Tasking* will be assessed by performing two tasks concurrently (motor and cognitive). For the motor task, we will use the Box & Blocks Test (BBT; Mathiowetz et al., 1985), a standardized assessment that has been widely used to assess manual dexterity, which is an important component of functional capacity (Canny et al., 2009; Hebert et al., 2012). The participant is asked to grasp and move 1-inch square wooden blocks from one side of an 8-in square box over a wooden partition to the other side within one-minute. The number of blocks transferred in 1 minute is registered. This test will be performed first by the dominant and then by the non-dominant hands. Lower scores indicate greater upper-extremity impairments. The BBT's psychometric properties have been well established in several adult populations (Kontson et al., 2017). For the single cognitive task, the participants will be asked to count by subtracting a number (e.g., 7 beginning from 399) and then to keep subtracting the same number from his/her answer in 1 minute. The order of the dual task assessment will be the following order (1 minute for each task): single cognitive task, single motor task with dominant hand, single motor task with non-dominant hand, dual motor-cognitive task with dominant hand, dual motor-cognitive task with non-dominant hand.

- *Cognitive flexibility* will be assessed by the Color Trail Test (**CTT**; D’Elia et al., 1996) a paper and pencil test of visual attention timed neuropsychological test. The CTT 1 consists of 25 circled numbers from 1 to 25 (even numbers in a yellow background and odd numbers in a pink background). The participant will be asked to rapidly connect the circles in consecutive order. The CTT2 consists of double the stimuli as the CTT1 with two sets of the 25 numbers in each color (pink and yellow). The participant will be asked to connect the numbers in ascending order alternating between the two-color sets. Scoring is calculated by measuring completion time (up to 240 seconds).

c. *Cognitive performance-based* assessment will be assessed by the Weekly Calendar Planning Activity (**WCPA**; Toglia, 2015). WPCA is a paper-and-pencil, performance-based

assessment that examines the influence of subtle executive function difficulties on person’s ability to perform a multiple-step activity. A randomly ordered list of 17 appointments is presented to the participant who is asked to schedule them using a 1-week calendar.

while adhering to five rules Scores include measures of accuracy, number of appointments entered, planning time (time from the beginning of the assessment until the first appointment is scheduled), total time, efficiency (calculated from the accuracy and total time), error types, number of rules followed out of the five given, and number of strategies used.

d. Perceived cognitive executive functioning

- *Cognitive Self Efficacy* (**SE**) will be assessed by the Cognitive Self Abilities Scale CogPCA (FACT-Cognitive Function Version 3). [The](https://www.facit.org/) CogPCA scale includes 7 statements with responses given on a 5-point Likert scale (from 0, never; to 4, several times a day). The score range= 0–28 with higher scores indicating higher difficulties.

*- Perceived Cognitive Impairment* will be assessed by the Perceived Cognitive Impairment scale – PCI (FACT-Cognitive Function Version 3; Wagner et al., 2009). The PCI scale includes 18 statements with responses given on a 5-point Likert scale (from 0, never; to 4, several times a day). The score range= 0–72 with higher scores indicating higher difficulties.

*- Three open-ended questions* (pre chemo "since diagnosis" and post chemo "since treatment"). The questions regarding person's changes in cognitive functioning and the consequences of these changes on his/her daily functioning will be presented on a sheet of paper and they will be asked to write their answers bellow together with the accessor.

1. *Emotional status* will be assessed by the Emotional Well-Being subscale (EWB; Cella et al., 1993) from the FACT-G (General) questionnaire (https://www.facit.org/). The EWB scale includes six statements with responses given on a 5-point Likert scale (from 0, not at all; to 4, very much). The score range= 0–24 with higher scores indicating higher emotional deficits.
2. *Fatigue* will be assessed by the Functional Assessment of Chronic Illness Therapy – Fatigue (FACIT-F) (Version 4; <https://www.facit.org/> ). The FACT Fatigue includes 13 statements with responses given on a 5-point Likert scale (from 0, not at all; to 4, very much). The score range= 0-52 with higher scores indicating more fatigue.
3. *Demographic and medical data Questionnaire* will include the following details: age, education, sex, marital status, number of children, years of education, work status, dominant hand, socioeconomic level (income level), type/stage of cancer, disease characteristics (e.g., size of tumor, number of affected lymph nodes), details of treatments received (e.g., types of surgery chemotherapy regimens, date of chemo commencement, number of cycles completed.

In addition, participants will be asked if we can contact them in the near future to perform a semi-structured interview: "do you agree to participate in an additional individual interview in the future as part of this study?"

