# **Statistical analysis**

# *Quantitative data analysis* will be performed by SPSS version 27. Descriptive statistics will be used to describe the study population and outcome measures. Normal distribution of the variables will be verified using Shapiro Wilk test. To compare between pre- and post-chemotherapy assessment: for normally distributed variables, paired t-tests will be used; when data are not distributed normally and scales of measurements are ordinal, non-parametric tests will be used; for the primary outcome (COPM, an ordinal scale), the Wilcoxon Signed Ranks test will be used.

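### The Emotional Well-Being score is given a direction that conflicts with its name, with no reversal rule, so emotional status could be read backwards in hypotheses 1a and 2a

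*Protocol*

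**What the plan says.** In the Protocol, section CRF and Measures (Appendix 1), emotional status "will be assessed by the Emotional Well-Being subscale" of the FACT-G. The response format is: "The EWB scale includes six statements with responses given on a 5-point Likert scale (from 0, not at all; to 4, very much". The range and direction follow: "The score range= 0–24 with higher scores indicating higher emotional deficits". No readable section gives a list of reversed items or a transformation of the total.

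Two hypotheses under Hypotheses according to aims depend on the direction of this score. In 1a, "emotional symptoms and fatigue will significantly worsen compared with pre chemotherapy". In 2a, before chemotherapy, "daily functioning will be mostly explained by higher emotional symptoms and fatigue". The outcome in the 2a regression is the COPM, whose performance rating runs upwards: "1=not able to do at all, 10=able to do extremely well".

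Under Statistical analysis, the pre/post comparison is a paired test ("for normally distributed variables, paired t-tests will be used", otherwise a non-parametric test). Emotional status enters the regression if it correlates significantly with daily performance.

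**The concern.** The name of the instrument says that a high score is good; the scoring sentence says that a high score is bad. Both can be true only if some scoring step turns one into the other, or if the six statements are worded as distress and summed as they stand. The protocol states neither.

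EWB is the only quantitative emotional measure in the study. It alone carries the emotional part of 1a and one of the two explanatory constructs in 2a. Both hypotheses are about direction. An analyst who receives a score built as well-being, and follows the protocol's sentence, would report a fall as fewer emotional deficits. The same analyst would read a positive slope on COPM as more deficits going with better functioning.

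**Working it through.** **1. The stated range.** Six items scored 0 to 4 give a minimum of 6 × 0 = 0 and a maximum of 6 × 4 = 24. This reproduces the protocol's 0–24. The range is the same whichever way the score runs, so it cannot settle the direction.

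**2. What the raw sum means depends on the item wording.** Let j of the six items be positively worded and none be reversed. The best emotional state then scores 4j and the worst scores 4(6 − j), so best minus worst is 8j − 24.

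| j | worst state | best state | best − worst |
|---|---|---|---|
| 0 | 24 | 0 | −24 |
| 1 | 20 | 4 | −16 |
| 2 | 16 | 8 | −8 |
| 3 | 12 | 12 | 0 |
| 4 | 8 | 16 | +8 |
| 5 | 4 | 20 | +16 |
| 6 | 0 | 24 | +24 |

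Among unreversed sums, the protocol's sentence fits the full 0–24 range only at j = 0. The name fits it only at j = 6. The value of j is not visible in the documents.

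**3. What a wrong direction does.** Let X be the score as well-being and X′ = 24 − X the score as deficits.

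- Pre/post: the change in X′ is minus the change in X, with the same SD, so t′ = −t and the two-sided p-value is the same.
- Regression: a + bX = (a + 24b) − bX′. The slope changes sign; R², the p-value and the significance of the correlation that decides entry do not.

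An illustration on simulated data, with every input assumed: 50 pairs, pre-chemotherapy well-being with mean 17 and SD 4, a true fall of 2 points with noise SD 4, and COPM = 5 + 0.15 × EWB plus noise with SD 1.

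| | scored as well-being | reflected (24 − X) |
|---|---|---|
| mean change | −2.42 | +2.42 |
| t | −5.05 | +5.05 |
| slope on COPM | +0.107 | −0.107 |
| R² | 0.139 | 0.139 |

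The left column is a worsening and a sensible association. Read as deficits without reflection, the same numbers become an improvement and an association of the wrong sign.

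**4. Neighbouring scales in the same section, set against their printed forms.**

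- *CogPCA.* The text says that higher means more difficulty and gives a frequency response set from never to several times a day. The printed Hebrew form carries ability statements, such as being able to concentrate, coded 0 for not at all to 4 for very much. An unreversed sum therefore rises with ability. Over the seven items that the text states, full ability scores 7 × 4 = 28 and none scores 0, which is the reverse of the stated direction.
- *Fatigue.* The text says 0–52 (13 × 4 = 52), with higher meaning more fatigue. Two of the 13 printed items are positively worded: An5 (has energy) and An7 (able to do usual activities). They are coded the same way as the rest. Unreversed, the most fatigued pattern scores 11 × 4 + 2 × 0 = 44, and the least fatigued scores 11 × 0 + 2 × 4 = 8. The span is 44 − 8 = 36 points instead of 52.

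So for two scales whose forms can be read, the stated direction or range holds only with a reversal that the text does not mention.

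**The case against.** A subscale's title names a construct and does not prove how a sum of responses runs. The protocol does fix a direction, and that direction matches the emotional symptoms of its hypotheses. If the six statements are worded as distress and summed as they stand, or the total is reflected, the sentence is right. For the perceived cognitive impairment scale the visible form does run as the text says. The EWB form may be among the figures that are not shown, and item-level scoring is often left to an analysis plan or a scoring manual. EWB is a secondary measure, and an implausible sign might well prompt a check.

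Most of this stands, and it sets the limit of the point. A reader might infer that the EWB direction is shown to be wrong, or that a full sign reversal will occur. The documents do not support that without the items. A reader might also want to attach a probability by computing power for 50 pairs. That would rest on effect sizes that the protocol does not give, and would apply only if the score is in fact misread. Nor do differences between stated and printed item counts in the FACT-Cognitive scales say anything about EWB, whose own arithmetic reconciles.

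The objection does not remove the conflict itself. The protocol does more than stay silent on scoring: it commits to a direction that its own name for the measure contradicts. The CogPCA and fatigue forms show that direction statements in this section cannot be taken on trust. An implausible sign is also a weak safeguard, because p-values and R² would look normal.

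**Conclusion.** The point holds in a limited form. The stated EWB direction conflicts with the construct named, and nothing readable reconciles them. Whether the computed score will actually be misread cannot be determined from the documents.

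If the score is built as well-being and read as deficits, the emotional conclusion in 1a and the sign of the EWB–COPM association in 2a are reversed. Under that pure reflection, two-sided p-values, R² and entry into the regression do not change. If instead the items are mixed in wording and summed without reversal, the score is compressed or even uninformative, and significance could change too; the size cannot be given without the items. The expected sign in 2a assumes the natural reading that more emotional symptoms go with poorer functioning.

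The primary pre/post COPM comparison is not touched in any of these cases. The correction is worth making before analysis because it is cheap and the error would be hard to see afterwards.

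**What to change.** Before any analysis, check the wording of the six EWB items on the Hebrew form in use and list any that are reversed. Then correct the measures section to one direction and state the signs that follow:

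- EWB as named: 0–24, higher meaning better emotional well-being. Hypothesis 1a then expects a fall, and 2a a positive coefficient with COPM.
- Or a derived emotional-symptoms score equal to 24 minus EWB. Hypothesis 1a then expects a rise, and 2a a negative coefficient.

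Apply the same check to CogPCA (direction and response set) and to fatigue (treatment of An5 and An7), and make the scoring syntax match. The cost is a few sentences and a syntax check, with no new data or participants.
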